### Statistical analysis plan

First, a cumulative incidence of allograft failure will be calculated. To define the best time for retransplant, different strategies may be implemented, based on the collected data at study end. As first choice, we will first draw a Kaplan–Meier for each risk stratum (i.e., each graft subtype). Then, we will analyze all potential risk factors for AF in each subtype by univariate and multivariate Cox regression models. Finally, we will implement these results in a temporal algorithm based on Cox curves to identify potential time windows for retransplant. In the case of multiple drops in the initial KM curves of similar duration, we will build the algorithm so to uniform the duration of each time-window. Alternatively, we can implement a change-point analysis model derived from Kaplan–Meier estimation of the survival function followed by the least-squares estimation of the change point [51], or a wavelet analysis of change-points based on a non-parametric hazard model [52]. We could also determine the different time windows by using an extension of Glazer’s method, using a mixture of two gamma distributions, hypothesizing two or more turning points [53]. Another possibility is represented using a Bayesian approach to the problem of hazard change with unknown multiple change-points by implementing a stochastic approximation Monte Carlo algorithm for efficient calculation of the posterior distributions [54]. Particularly used in graft failure prediction. Also, a joint latent change-point class model could represent a potential way to improve the prediction of fixed time windows for retransplantation [55, 56]. All these potential applications would depend on the data distribution at the end of data collection and events observed during the follow-up period.

Notably, since the percentage of adoption of machine perfusion is expected to be one of the main differences between the two study segments, although heterogeneously worldwide, models will be adjusted according to this parameter.i.Subgroups and interactions.

The incidence of AF at 90 and 365 as well as the incidence of death at 90 and 365 days will be calculated. Differences between the three main graft types subgroups will be investigated using either one-way ANOVA, if normally distributed, or otherwise by the Kruskal–Wallis non-parametric test. The Chi-square test will instead assess differences between qualitative variables. The significance level will be set at < 0.05.

Kaplan–Meier curves will be calculated and differences will be investigated through log-rank test.ii.Missing data management.

A. Missing data in the calculation of the area under the curve (AUC) and the slope of the kinetic model will be addressed as follows:Patients who were retransplanted or died before day 10 were excluded from the calculation of the AUC and slope because of the real impossibility to calculate the score which is by definition computed at day 10. The number of this subgroup will be reported in the flow diagram of the patients. These cases will be excluded from the patient population utilized for the development of algorithms. However, these cases will be considered for the calculation of the outcome measures (overall % of AF, % failure at 90 days, % failure at 365 days, length of stay, overall graft survival, and overall patient survival).Patients who have been discharged between day 8 and 10 and do not have the day 10 determination (missing value referring to the day 10 determination of AST or Platelet count or bilirubin). In these cases, the values at day 7 will be used. The number of these cases will be reported in the flow diagram. We are aware that this approach might overestimate the value of the AUC and consequently the score’s value. However, as the number of patients without day-10 data is expected to be small, we believe that the effect will be minimal and not relevant for the purpose of the study.Patients with missing data at day 2, or day 3 will be excluded, being impossible the calculation of the score. Their number will be reported in the flow diagram.Patients with missing data at day 4 will be included. The AUC and the slope will be calculated using the trapezoid method not including day 4. Their number will be reported in the flow diagram.Patients with missing data at day 5 will be included. The AUC and the slope will be calculated using the trapezoid method not including day 5. Their number will be reported in the flow diagram.Patients with missing data at day 6 will be included. The AUC and the slope will be calculated using the trapezoid method not including day 6. Their number will be reported in the flow diagram.Patients with missing data on two consecutive days (day 4 and 5, or day 5 and 6, or day 6 and 7) will be included. The AUC and the slope will be calculated using the trapezoid method not including the two consecutive missing days. Their number will be reported in the flow diagram.Composite missing data (e.g., AST from one day and bilirubin from a different day) will follow the above-mentioned rule. Their number will be reported in the flow diagram.Missing data in the descriptive analysis will be reported. Parameters of interest with percentage of missings higher than 8% will not be reported in tables neither will be considered for further univariate or multivariate analysis.Loss to follow-up.

The count of cases lost to follow-up will be reported together with in the numbers at risk tables below the Kaplan–Meier curves.

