Secondary (#5)	To identify the best-time for re-transplant (after stratification according to the post-operative weeks, months, trimesters);
Secondary (#6)	To investigate differences in the incidence of allograft failure and ischemic cholangiopathy at 90 and 365 days according to standard DBD, DCD and high- risk DBD, LD donor grafts;
Secondary (#7)	To evaluate the effect of mitigation strategies on the precipitating factors of Allograft Failure at 90 and 365 days;
Secondary (#8)	To investigate the association of kinetic algorithms with development of post- LT complications (acute kidney injury, ischemic cholangiopathy, other complications);
Secondary (#9)	To identify risk factors for mortality that may contraindicate re-transplant;
Secondary (#10)	To investigate the impact of donor-to-recipient gender match on LT outcomes

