### Outcome measures

Allograft failure (AF) was defined as graft failure (leading to retransplant or death) for any reason at day 90 and at day 365 after LT. This definition also captures all late-occurring AFs (also known as delayed non-function) [34, 35] We consider as AF determinants all those events potentially affecting the process of graft function recovery, independently if they were strictly associated with ischemia–reperfusion injury. Indeed, vascular (thrombosis of the hepatic artery or portal vein), biliary, toxic, and major hemodynamic events will be included, because any of them can interact with parenchymal dysfunction, affecting graft function recovery and favoring graft failure and death.

Other outcome measures are comprehensive complication index, intensive care unit length of stay, hospital length of stay (LoS), and cholangiopathy-free survival at 90 and 365 days, graft and patient survival at 90 and 365 days,

The prospective cohort dataset includes 297 data entries and 27 calculated parameters (see supplementary material 1). Variable domains are:identification datadonor characteristics datarecipient preoperative datagraft histology dataintraoperative datarecipient postoperative datastudy endpoints dataoutcome and follow-up data.

The electronic Case Report Form (eCRF) was developed using the REDCap ver 10.0.21 software hosted at https://redcap-irccs.policlinicogemelli.it/. The eCRF allows easy calculation of scores including L-GrAFT and EASE scores.

The REDCAP software performs de-identification and encryption of the data.

The retrospective segment dataset includes 241 variables (supplementary material) to be collected from each center’s previously existing databases.

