## Discussion

This protocol refers to the first global study on liver transplantation outcomes. The study design includes several objectives based on LT practice worldwide, with centers participating in a balanced manner depending on their country’s location and activity. In addition to cross-sectional information, we expect to acquire a large volume of data to develop new models for predicting AF at different time points.

First, it will be paramount to build a new model for predicting early AF (i.e., 90-day post-LT allograft failure) based on a multicenter international comprehensive retrospective and prospective data collection. The work set by the steering committee stands on the background of the existing kinetics-based scores (L-GrAFT and EASE) constructed from a single center and a multicenter two-nation setting, respectively. Compared to these two scores, the models we aim to develop imply the advantage of a wider setting (60 centers, 21 countries, from 6 world areas) and a prospective patient enrollment. In addition to standard transplant outcome measures (graft failure and patient death at 90 and 365 days), we will pay attention to hospital and ITU length of stay, the incidence of weaning/extubation failure [57], as well as surgical complications. [58–60] Furthermore, we expect the study to allow us to develop and validate model(s) with increasing predictive accuracy from the 3rd to 7th postoperative day, making them more usable for all-day practice, bringing forward the availability of prognostic tools in the first few days after LT. We expect these tools to be able to weigh the risk of death without retransplantation and aid the decision-making processes for transplant physicians.

The presence of a retrospective study segment composed of high- and medium-volume centers guarantees a second-layer control of the applicability of previous models as well as the potential backward test of new models to real-world scenarios. The existing kinetic-based scores will be tested on the retrospective data with the aim of validating them on a large scale on a broad variety of liver transplant centers across different countries.

Second, we extended the evaluation time to 365 days, with the intent of capturing those failures occurring at a later stage. Late failure is increasingly seen nowadays due to the growing utilization of DCD and ECD grafts and the subsequent loss of grafts from ischemic cholangiopathy.

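### Secondary objective #5: windows read from allograft-failure curves show when retransplants and deaths occurred and cannot identify the best time for retransplant

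*Protocol article*

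**What the plan says.** Table 2 of the Protocol article (Introduction) gives secondary objective #5: "To identify the best-time for re-transplant (after stratification according to the post-operative weeks, months, trimesters".

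The section Outcome measures fixes the endpoint: "Allograft failure (AF) was defined as graft failure (leading to retransplant or death) for any reason at day 90 and at day 365 after LT".

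The Statistical analysis plan opens with "First, a cumulative incidence of allograft failure will be calculated". For the best time to retransplant it then sets out a first choice in three steps:

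1. "As first choice, we will first draw a Kaplan–Meier for each risk stratum (i.e., each graft subtype".
2. Univariate and multivariate Cox models of risk factors for AF within each subtype.
3. The plan to "implement these results in a temporal algorithm based on Cox curves to identify potential time windows for retransplant". Drops in the Kaplan–Meier curves shape the windows.

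The alternatives listed are a change-point model from the Kaplan–Meier estimate, a wavelet analysis, a gamma-mixture extension, a Bayesian multiple change-point model and a joint latent change-point class model. On choosing among them the text says: "All these potential applications would depend on the data distribution at the end of data collection".

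The section Quantitative variables adds that predictors of allograft survival and of patient survival at 90 and 365 days will be assessed, and that these characteristics will feed the algorithms for the retransplant window. Objective #9 covers mortality risk factors that may contraindicate retransplant.

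**The concern.** The best time for retransplant is a comparative question. Among patients alive with the first graft at a given time, is later survival better if they are retransplanted now than if they are not yet retransplanted? Answering it needs survival after retransplant and a comparison group still waiting.

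The AF curve supplies neither. Retransplant ends follow-up for AF by counting as the failure. A steep stretch of the curve therefore marks a period in which centres chose to retransplant, or in which patients died, or both. Windows built on such stretches reproduce existing practice and the timing of deaths. Under the label of objective #5 they would be read as the best time to act.

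**Working it through.** **Which endpoint the first choice uses.** The Kaplan–Meier sentence does not name its endpoint. The text before it speaks of the cumulative incidence of allograft failure and the sentence after it of risk factors for AF. The endpoint is therefore AF, that is, retransplant or death.

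**What the curve contains.** For each patient AF time = min(time to retransplant, time to death). Death after retransplant lies beyond that minimum and never enters. Cox models of AF condition the same quantity on covariates and do not bring it in.

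**Illustration.** The document gives no event count, power or split of AF for objective #5, so there is no stated figure to reproduce. A simulation of 200,000 patients used these assumed inputs:

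- death before retransplant: exponential, mean 365/0.06 days;
- retransplant: exponential, mean 365/0.04 days, except that 5% of patients have a retransplant time uniform between days 2 and 30;
- AF time: the smaller of the two;
- probability of death after retransplant: scenario A, 0.2 if retransplanted by day 30 and 0.5 if later; scenario B, the reverse.

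| | Scenario A | Scenario B |
|---|---|---|
| AF by day 7 | 1.06% | 1.06% |
| AF by day 30 | 5.84% | 5.84% |
| AF by day 90 | 7.35% | 7.35% |
| AF by day 365 | 14.17% | 14.17% |
| Death after retransplant by day 30 | 19.9% | 49.7% |
| Death after retransplant on days 31–365 | 50.1% | 20.3% |

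The AF columns agree by construction, because post-retransplant death is not part of AF. Every drop falls in the same place while the effect of timing is reversed. A larger sample would not separate the two.

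**Whether other parts of the plan make the comparison.**

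- The listed alternatives, as described, locate changes in a survival or hazard function or predict time windows. None is described as comparing patients retransplanted at a given time with those not yet retransplanted.
- The patient-survival analysis in Quantitative variables looks for predictors. It does not set retransplant against waiting at a given time.
- Objective #9 concerns mortality risk factors, again without that comparison.

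**How much information a suitable analysis would have.** The overall AF rate assumed in Study size and power calculations is 6%. It is read here as a 90-day rate, because the incidence figures listed just above it are mostly 90-day figures.

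- Both segments: 750 + 4200 = 4950 patients; 4950 × 0.06 = 297 AF events.
- Retransplants among them are not stated. At assumed shares of 20%, 50% and 80%: about 59, 148 and 238.
- Table 3 plans the postoperative assessment of factors favouring or contraindicating retransplant only in the prospective segment: 750 × 0.06 = 45 AF events. At the same shares: 9, about 22, and 36 retransplants.

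**The case against.** Much can be said for the plan.

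- **Patient survival has a role.** Its predictors feed the window algorithms, death at 90 and 365 days is tabulated separately, and objective #9 addresses mortality. The window algorithm is thus not described as resting on AF alone. This stands as a limit on wording, but none of these items compares survival with and without retransplant from a given time.
- **The simulation follows from the definition.** It tests the AF curve and not a full algorithm with survival predictors added. That is correct, and it is offered only as an illustration.
- **A condensed article may leave detail to a fuller plan.** Details of the algorithm, yes. But the article itself fixes the endpoint and the first-choice method, and the mismatch lies between those two and the objective.
- **The aim is modest.** The text speaks of potential windows, in an observational study that changes no centre's practice, under one of several secondary objectives. This limits the reach of the point, but Table 2 still names the best time as the target.

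Stronger readings are tempting and the document does not support them.

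- A reader might infer that every alternative method uses AF. Their endpoint is not named, so that is inference.
- A reader might infer that the methods are six unranked options. A first choice is named; what depends on the data is any move away from it.
- A reader might take the Discussion's hope of weighing the risk of death without retransplantation as the aim this analysis fails. That sentence follows one on the day 3 to 7 prediction models and refers to those tools.
- A reader might want a count of events per window. The number of living-donor grafts is not given, and weeks, months and trimesters overlap, so no such count can be derived.

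**Conclusion.** The point holds for secondary objective #5. The stated first choice reads windows for retransplant from an endpoint that includes retransplant. It therefore describes when retransplants and deaths took place and cannot identify the best time. The alternatives and the patient-survival analyses, as described, do not supply the missing comparison.

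The size is categorical: the curve carries no information on the effect of timing, whatever the sample. The direction of any error in the reported windows cannot be known from the curves. The conclusion rests on the text's definition of AF and on reading the Kaplan–Meier endpoint as AF from its context; it does not depend on the simulated rates or the assumed retransplant shares.

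The analysis and claims for this objective need correcting. AF prediction, score validation and the two primary objectives are not affected. Nothing here implies a clinical rule on when to retransplant.

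**What to change.** 1. Label the AF Kaplan–Meier, Cox and change-point windows as a description of when failures occur, and do not report them as the best time for retransplant.
2. For objective #5, take death from any cause as the outcome with retransplant as a time-dependent exposure. Alternatively, at fixed landmarks, compare later survival of patients retransplanted in the next interval with that of patients alive and not yet retransplanted.
3. Adjust for covariates known at the landmark. The day-10 score cannot serve at earlier landmarks: it is computed at day 10, and patients retransplanted or dead before then are excluded from algorithm development.
4. Pool graft types where events are few.
5. Name this as the primary method for the objective before the data are seen.
6. If it proves not estimable, reword objective #5 as descriptive.

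**Cost.** New wording and programming. Patient survival is already an outcome, and Table 4 allows retransplants to be enrolled when the first transplant was. The statistical cost is larger: intervals will be wide and confounding will remain, because retransplants are few and the factors favouring or contraindicating them are assessed only in the 750-patient prospective segment.

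### The method for defining retransplant time windows is chosen after the events are seen, with no stated criterion for concluding that no distinct window exists

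*Protocol article*

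**What the plan says.** Table 2 of the protocol article gives secondary objective 5 as "To identify the best-time for re-transplant (after stratification according to the post-operative weeks, months, trimesters". The Statistical analysis plan section opens this analysis by saying that "different strategies may be implemented, based on the collected data at study end".

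The first choice has three steps: a Kaplan–Meier curve for each graft subtype, univariate and multivariate Cox models, and then a plan to "implement these results in a temporal algorithm based on Cox curves to identify potential time windows for retransplant". One conditional sentence concerns the shape of the curves: "In the case of multiple drops in the initial KM curves of similar duration, we will build the algorithm so to uniform the duration" of the windows.

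Five alternatives follow:

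- a change-point model based on the Kaplan–Meier estimate, "followed by the least-squares estimation of the change point";
- a wavelet analysis of the hazard;
- an extension of Glazer's method with a mixture of two gamma distributions, "hypothesizing two or more turning points";
- a Bayesian model in which the number of change-points is unknown;
- a joint latent change-point class model.

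The paragraph closes on how one is picked: "All these potential applications would depend on the data distribution at the end of data collection and events observed during the follow-up period".

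**The concern.** Two features combine. The choice among six approaches is tied explicitly to the event pattern, and the section gives no criterion for choosing among them. It also gives no comparison with a hazard that has no change-point, and no wording for a negative result. The objective and the Quantitative variables section are both phrased as if a best time or window exists.

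A change-point estimator answers where a change lies, given that there is one. It does not answer whether there is one. If the second question is never put, objective 5 can report a window whose position reflects noise or the chosen method. The closing paragraph of the Discussion lists retransplant timing among the matters on which the study will focus, so a spurious window would be read as a substantive result.

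**Working it through.** **Figure in the plan.** The article gives no error rate, threshold or power for this analysis, so there is no stated figure to reproduce. The simulation borrows the 6% failure rate from Study size and power calculations and treats it as a day-90 rate. That rate does underlie the plan's own calculation: the Hanley–McNeil standard error at AUC 0.76, n = 4000 and 6% is 0.01838, so the interval is 0.76 ± 1.96 × 0.01838 = 0.724 to 0.796, as printed.

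**Inputs.** 6% failure at day 90 (plan). Follow-up to day 365 (plan). n = 750 and 4200 (the two segments). n = 300 is an assumed graft-subtype stratum. The 365-day rate is not given and follows from the assumed hazard shape.

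**Two hazards without a change-point.** Cumulative hazard at day 90: H(90) = −ln(0.94) = 0.0619.

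- Constant: H(365) = 0.0619 × 365/90 = 0.251, so failure by day 365 is 1 − exp(−0.251) = 22%.
- Smoothly falling Weibull, shape 0.5 (assumed): H(365) = 0.0619 × (365/90)^0.5 = 0.125, so failure by day 365 is 1 − exp(−0.125) = 12%.

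**Least-squares option.** The Kaplan–Meier cumulative hazard on days 1 to 365 is fitted by b1·d + b2·max(d − c, 0). The estimate is the day c with the smallest residual sum of squares, searched from day 7 to day 355 in four-day steps.

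| Hazard | n | Mean events | Location returned | 5th / 50th / 95th percentile (day) |
|---|---|---|---|---|
| Constant | 300 | 67 | 400 of 400 | 15 / 147 / 311 |
| Constant | 750 | 167 | 400 of 400 | 19 / 155 / 311 |
| Constant | 4200 | 932 | 300 of 300 | 19 / 167 / 315 |
| Weibull | 300 | 35 | 400 of 400 | 7 / 47 / 171 |
| Weibull | 750 | 88 | 400 of 400 | 15 / 43 / 87 |
| Weibull | 4200 | 492 | 300 of 300 | 31 / 43 / 63 |

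The 100% holds by construction, because a minimum over a grid always exists. The locations are the informative part. Under a constant hazard they cover most of follow-up and do not tighten with sample size. Under the smooth Weibull they do tighten, although no change-point exists, so a precise location is not evidence that one does. The location also depends on the assumed shape: with shape 0.31 (10% failure at day 90, 15% at day 365) the least-squares median was about day 20, against 43 to 47 above.

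**Gamma-mixture option.** No arithmetic is needed. At least two turning points are assumed before fitting.

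**Bayesian option.** It can return zero change-points if the prior allows it. For example, Poisson priors with means 0.5, 1 and 2 on the number of change-points put probability 0.61, 0.37 and 0.14 on zero. The article states no prior.

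**Effect of allowing a negative result.** A BIC rule comparing one change-point with none (piecewise-exponential likelihood, two extra parameters) was applied to the same settings. Under a constant hazard it declared a change-point in 9.0%, 5.8% and 0.3% of runs at n = 300, 750 and 4200. Under the smooth Weibull it still declared one in 97 to 100%. The comparison model must therefore include a smooth falling hazard.

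**The case against.** - **Not every option is bound to return a window.** This stands. A reader might infer that the rule as a whole always yields windows. The documents do not support that: the Bayesian model leaves the number of change-points open, a thresholded wavelet analysis could find none, and the text speaks only of potential windows. What remains is that a null from one method can be followed by a switch to another.
- **A first choice is named.** This also stands. It would be wrong to say that windows are simply read off drops in the Kaplan–Meier curves; the sentence on drops only makes window lengths uniform. But the Cox-based algorithm has no stated criterion for what counts as a window, and the choice still depends on the data.
- **A condensed article leaves detail to a full analysis plan.** This is fair for thresholds and priors. It does not cover the selection of method after the events are seen, which the article states outright.
- **A constant hazard is unrealistic.** The article describes early failures followed by later cholangiopathy losses. That is why the Weibull case matters more. Splitting early high risk from later low risk can be a useful description, but it is not evidence of a distinct window.
- **Objective 5 names strata of weeks, months and trimesters.** The analysis section does not use these strata, and they supply no rule for choosing a method.

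A reader might also infer a definite false-positive rate. A searched likelihood ratio judged at 3.84 gives 46% to 64% under a constant hazard, depending on the setup, but the plan contains no such test, so this is not its error rate. Nor do the documents say that the windows themselves will be a decision rule; the Introduction's remark on guiding retransplant decisions concerns the comprehensive prediction model.

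**Conclusion.** The point holds in limited form. The protocol article allows the window method to be selected after the data and events are seen, and it states no criterion for concluding that no distinct window exists. Two of the six listed approaches, least squares and the gamma mixture, give change-points regardless of the truth; the others are either undefined on this point or may return none. The simulated locations rest on the assumed hazard shapes, 365-day rates and stratum size, and show how far a location can mislead. The certainty that least squares returns one does not depend on those assumptions. This affects a secondary objective and leaves the prediction-model objectives untouched.

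**What to change.** In the Statistical analysis plan section, name one primary method before data lock, and make it one that allows zero change-points, for example a piecewise hazard model with 0, 1 or 2. Compare it with a smooth hazard without change-points (Weibull or spline, not only a constant hazard) by parametric bootstrap or BIC. Report a bootstrap interval for each change-point, and state that finding no distinct window is a possible conclusion. Keep the remaining methods as labelled sensitivity analyses.

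Report consistency between the prospective and retrospective segments descriptively. It should not be a condition for declaring a window: 750 prospective patients at 6% give about 45 failures by day 90 (750 × 0.06) before splitting by graft subtype, and the segments differ in centre volume, era and use of machine perfusion.

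The cost is revised wording and a little more computing, with no new data. The downside is that the study may have to report that no window was found.
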